**Figure 3 F3:**
[figure not shown]
Recruitment and study procedures. AI :Aromatase Inhibitors; APA :Adapted Physical Activity.

### Outcomes

#### Primary outcome

The primary outcome will be the score for the most intense musculoskeletal pain, assessed with the Nordic-style questionnaire, 6 months after the introduction of the AI (T2).

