### Study objectives

The primary study aim is to compare the prevalence of musculoskeletal pain after 6 months of AI therapy between patients who started a personalised APA programme at the start of their care pathway and those receiving usual care.

The secondary objective is to explore contextual factors influencing the implementation of the APA programme in real-world oncology care, including perceived barriers and facilitators, based on quantitative and qualitative data collected from both patients and healthcare professionals.

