### Sample size

#### Sample size for the primary outcome

The expected prevalence of AIMSS in the standard care group is approximately 40%. We hypothesise a 50% reduction (20%) in the experimental group with early implementation of APA.^20^ Considering an alpha risk of 5%, a power of 80% and a two-sided hypothesis, 82 patients per arm will be required. Assuming 10% unusable data, a total of 182 patients will be included.

Sample size for the qualitative component of the mixed-methods study (secondary implementation aim).

The principle of theoretical saturation will guide the sample sizes of the two groups (patients and healthcare professionals), once the collected data are sufficient to explain the phenomenon. Data collection, conducted progressively and in parallel with analysis, will define the final sample size.^21^

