#### Primary data collection

The prevalence of musculoskeletal pain will be assessed using the Nordic-style questionnaire, a validated tool for detecting musculoskeletal disorders. It consists of closed-ended questions and can be used as a self-reported questionnaire.

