### Data analysis

#### Quantitative data analysis

The statistical analysis will be performed on the intention-to-treat population.

For the primary objective, the maximum intensity of musculoskeletal pain at 6 months (T2) will be compared between groups using parametric (eg, t-test) or non-parametric (eg, Wilcoxon-Mann-Whitney) tests, depending on data distribution.

Secondary objectives include evaluating the intervention’s effects on outcomes such as physical health, psychosocial well-being and treatment adherence. Analyses will include: (1) between-group comparisons at specific time points (T0, T1, T_APA_, T2), (2) between-group comparisons of change over time (eg, T0–T1, T1–T2) and (3) within-group longitudinal changes across time points.

Univariate and multivariate logistic regression models will explore factors associated with the occurrence of AIMSS. Qualitative variables will be compared using χ^2^ or Fisher’s exact test, as appropriate.

All analyses will be two-sided with a significance threshold of p<0.05. Missing data will be handled using appropriate statistical methods. Analyses will be conducted using R software (R Foundation for Statistical Computing, Vienna, Austria).

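### The primary aim and the 182-patient sample size concern a prevalence (40% vs 20%), but the declared primary outcome and test concern a maximum pain score, so the stated 80% power does not belong to the planned analysis

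*Protocol article*

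**What the plan says.** Three parts of the protocol article describe a binary question, as does the aim given in the Abstract.

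- Study objectives: "The primary study aim is to compare the prevalence of musculoskeletal pain after 6 months of AI therapy".
- Primary data collection: "The prevalence of musculoskeletal pain will be assessed using the Nordic-style questionnaire".
- Sample size for the primary outcome: "The expected prevalence of AIMSS in the standard care group is approximately 40" per cent, and "We hypothesise a 50% reduction (20%) in the experimental group with early implementation of APA". With a two-sided alpha of 5% and 80% power, this gives 82 per arm, and 182 in total after allowing for 10% unusable data.

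Two parts describe a score.

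- Primary outcome: "The primary outcome will be the score for the most intense musculoskeletal pain, assessed with the Nordic-style questionnaire", measured at T2.
- Quantitative data analysis, where the main comparison is set out: "the maximum intensity of musculoskeletal pain at 6 months (T2) will be compared between groups using parametric (eg, t-test) or non-parametric (eg, Wilcoxon-Mann-Whitney) tests". Which of the two is used follows from how the data are distributed.

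The same analysis section also names chi-square or Fisher tests for qualitative variables, and logistic regression for factors associated with AIMSS. Neither is tied to the primary objective.

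**The concern.** A trial has one confirmatory comparison. Here the quantity named in the aim and used for the sample size is not the quantity that will be tested. Two things are at stake.

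First, the primary p-value would not answer the stated aim. A maximum score can differ between arms when the proportion with pain does not, and the proportion can halve without a clear difference in the score.

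Second, the 80% power was derived for a different endpoint and a different test. Nothing in the article lets a reader work out the power of the analysis that is planned.

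There is a smaller mismatch within the prevalence passages. The aim names musculoskeletal pain, while the 40% and 20% are rates of AIMSS. The Background describes AIMSS as a syndrome with pain as its most common symptom, so the two need not have the same prevalence.

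**Working it through.** **Step 1. Reproduce the stated sample size.** Inputs from the sample-size section: p1 = 0.40, p2 = 0.20, two-sided alpha 5% (z = 1.960), power 80% (z = 0.8416). The mean proportion is 0.30. The usual two-proportion formula with pooled variance under the null is

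n per arm = [1.960 × √(2 × 0.30 × 0.70) + 0.8416 × √(0.40 × 0.60 + 0.20 × 0.80)]² / (0.40 − 0.20)²

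= [1.960 × 0.6481 + 0.8416 × 0.6325]² / 0.04

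= (1.2702 + 0.5323)² / 0.04 = 3.249 / 0.04 = 81.2, rounded up to **82**.

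Power at 82 per arm is 80.4%. For the total, 164 / 0.90 = 182.2, which agrees with 182 within rounding. The arithmetic is sound, and it is that of a test of two proportions.

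**Step 2. What 82 per arm means for a score.** For a t-test, the standardised difference detectable with 80% power is about (1.960 + 0.8416) × √(2/82) = 2.8016 × 0.1562 = 0.438, or **0.44 SD** with the exact noncentral t. The article states no such difference. Power at 82 per arm for a range of assumed differences:

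| Assumed difference (SD) | t-test power |
|---|---|
| 0.2 | 25% |
| 0.3 | 48% |
| 0.4 | 72–73% |
| 0.5 | 89% |
| 0.6 | 97% |

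**Step 3. Do the 40% and 20% rates fix the power of the score test?** They do not. The scenarios below are simulated with 82 per arm and 4,000 runs, and each keeps 40% vs 20%. The 0–10 scale and all score distributions are assumptions, because the article gives none. In the first two rows, non-cases score 0, and control cases are half mild (1–3) and half severe (4–10).

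| Assumed pattern | Two proportions | t-test | Wilcoxon |
|---|---|---|---|
| Only mild cases prevented | about 80% | 15% | about 60% |
| Only severe cases prevented | about 80% | 99.8% | 92% |
| Non-cases 0; cases about N(5, 2) in both arms | 81% | 74% | 80% |
| Non-cases about N(3, 2.5); cases about N(5, 2.5) | 81% | 16% | 16% |
| Normal score shifted by 0.59 SD, cut at the 40% point | 80% | 96% | 96% |

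The proportion test stays near 80% throughout. The score tests do not.

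**Step 4. Can the two analyses disagree?** Assume 40% cases in both arms, with scores of 4–10 in control cases and 1–4 in experimental cases. The proportion test rejects in 5% of runs, as it should under equal prevalence. The t-test rejects in 99% and the Wilcoxon test in about 50%.

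**Step 5. Does 182 survive a change of case definition?** Only if the rates stay near 40% vs 20%. The Step 1 formula at other assumed rates gives 121 per arm for 30% vs 15% (120.5 rounded up), 93 for 50% vs 30%, and 97 for 60% vs 40%.

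**The case against.** The strongest reply is that this is a condensed article. Its tests are given only as examples, and the cut-off, the single model and the rule for choosing a test are commonly left to an analysis plan or full protocol. That is right for those details, and none of them is raised here as a fault in itself. A binary AIMSS variable is also foreseen, since the analysis section models its occurrence by logistic regression. However, that line is not linked to the primary objective, whereas the score comparison explicitly is. An analysis plan could follow one version only by contradicting the other.

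A second reply is that the simulated figures come from assumptions and not from the article. This also stands. The article gives no score range or severity bands, and nothing on how many patients will score zero. A reader might infer from the 15% figure that the trial is underpowered. The documents do not support that: the mirror-image assumption gives 99.8%, and a pure shift gives 96%. The simulations show only that the power is undetermined.

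A reader might also infer that the sample size was miscalculated. It was not, as Step 1 shows.

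**Conclusion.** The contradiction is in the text and does not depend on any assumption: the aim, primary data collection and sample size concern a prevalence, while the primary outcome and primary test concern a maximum score. The stated 80% power (80.4% when recomputed) is a property of a two-proportion comparison that is not planned as primary. The power of the planned score test cannot be determined from the article and may be well above or below 80%; the range of about 15% to over 99% rests on assumed score distributions. The planned test can also reach a different conclusion from a comparison of prevalence. This should be corrected before any T2 data are seen, because it concerns the trial's single confirmatory result.

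**What to change.** **Preferred.** Rewrite the Primary outcome and Quantitative data analysis sections to match the aim.

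- Primary outcome: the proportion of patients who are cases at T2. Use one construct, either musculoskeletal pain or AIMSS, and the same one in the objectives and the sample size. Base the case definition on the Nordic-style questionnaire and fix it before any T2 data are seen.
- Primary analysis: a comparison of two proportions, reporting the risk difference with its 95% CI.
- Make the maximum score a secondary outcome.

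The 182 patients and 80% power then stand, provided the chosen definition is expected to give about 40% vs 20%. Otherwise the sample size must be recalculated.

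**Alternative.** If the score is to remain primary, reword the Abstract, Study objectives, Sample size and Primary data collection for the score, and remove the claim of 80% power for 40% vs 20%. State instead that 82 per arm gives 80% power by t-test for a difference of about 0.44 SD, and justify whether that difference is worthwhile. The 0.44 SD is back-calculated from the sample size, so it is not a justification in itself. If a smaller difference matters, more patients are needed: 99 per arm for 0.4 SD and 175 for 0.3 SD, by the normal approximation.

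**Cost.** Protocol rewording under either option, and no new data collection. The power statement may become less favourable.

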#### Secondary outcomes: effectiveness aim

Secondary outcomes will evaluate the effects of the intervention on physical health and psychosocial well-being by assessing global pain, cognitive problems, physical condition, body composition and nutritional status, indicators of metabolic syndrome, heart rate variability, therapeutic adherence to the AI and adverse events related to the intervention. These outcomes will be assessed at four time points (T0, T1, T_APA_, T2) using validated questionnaires, clinical examinations and functional tests.

#### Secondary outcomes: implementation aim

The implementation of the APA programme will be evaluated using the Reach, Effectiveness, Adoption, Implementation and Maintenance (RE-AIM) framework, which is designed to assess both the public health impact of interventions and the processes underlying their implementation.^18^ All five RE-AIM dimensions will be examined to capture key factors influencing real-world applicability, using a combination of quantitative and qualitative data collected from participants and healthcare professionals throughout the study.

#### Secondary outcomes: risk factors for the development of AIMSS

The APIS study will investigate potential risk factors for the development of AIMSS by examining associations between clinical, demographic, treatment-related and psychosocial variables and the occurrence of musculoskeletal symptoms.

### Participant timeline

The assessment schedule for both groups is presented in table 1.

**Table 1 T1:** Schedule of study visits and assessments

	IV	T0	T1	T_APA_	T2
**Enrolment**					
Review of inclusion/exclusion criteria	**X**				
Study presentation/delivery of the participant information sheet	**X**				
Signature-informed consent	**X**				
**Randomisation**					
Group allocation		**X**			
**Intervention**					
Start of personalised APA protocol, **experimental group**		**X**			
Start of personalised APA protocol, **control group**			**X**		
**Assessments**					
Initial clinical assessments***	**X**				
Clinical assessments†		**X**	**X**	**X**	**X**
Anthropometric measurements‡		**X**	**X**	**X**	**X**
6MWT		**X**	**X**	**X**	**X**
Hand grip test		**X**	**X**	**X**	**X**
Pulmonary function test§§		**X**			
Cardiopulmonary exercise testing¶¶		**X**			**X**
Blood test****		**X**	**X**		**X***
24-hour Holter ECG monitoring††††		**X**			**X**
Self-Report Questionnaires‡‡		**X**	**X**	**X**	**X**
Self-directed physical activity follow-up: email or paper logbook§§		**X**	**X**	**X**	**X**
Data collected/implementation		**X**	**X**	**X**	**X**
Data collected/risk factors for the development of AIMSS			**X**		
Semi-structured interview					**X**
Monitoring of adverse events			**X**	**X**	**X**
Monitoring of APA-related adverse events			**X** EG	**X**	**X**

* Initial clinical assessments performed by the surgeon or APN: clinical examination, identification of barriers and facilitators to regular physical activity during the medical interview and assessment of absolute and temporary contraindications to adapted physical activity.

† Clinical assessments performed by the sports medicine physician.

‡ Anthropometric measurements: weight, height, BMI, waist circumference, four skinfolds.

§ Pulmonary function test: FEV1, PEF, VT, VC, RV, TLC, DLCO correction.

¶ Cardiopulmonary exercise testing: VO₂ peak, VO₂ max, maximal heart rate, VO₂ at ventilatory threshold -VT1-, cardiac output at VT1, heart rate at VT1, blood pressure, oxygen saturation.

** Blood test: lipid profile at V0 and V1 (V2 if abnormal value at V1), fasting insulin and fasting blood glucose at V0 (V1 if abnormal value at V0 and V2 if persistent abnormal value at V1), C-reactive protein at V0 (V1 and V2 if inflammation is suspected).

†† 24-hour Holter ECG monitoring: total spectral power.

‡‡ Self-Report Questionnaires (cf. table 2).

§§ Self-directed physical activity follow-up: type, intensity (Borg scale), duration, frequency of physical activity and adverse effects of PA.

.AIMSS, aromatase inhibitor-induced musculoskeletal symptoms; APA, adapted physical activity ; APN, Advanced Practice Nurse; BMI, body mass index; CG, control group; CRP, C-reactive protein; D, day; DLCO, diffusing capacity of the lung for carbon monoxide; EG, experimental group; FEV1, forced expiratory volume in 1 s; HOMA-IR, Homeostatic Model Assessment for Insulin Resistance; IV, inclusion visit; M, month; MWT, 6-minute walk test; PA, physical activity; PEF, peak expiratory flow; RV, residual volume; T0, pre-therapeutic phase; T1, initiation of the aromatase inhibitors; T2, 6 months after the initiation of the aromatase inhibitors; T_APA_, end of the 12-week APA programme; TLC, total lung capacity; VC, vital capacity; VO₂ max, maximal oxygen consumption; VO₂ peak, peak oxygen consumption; VT, tidal volume.

**Table 2 T2:** Summary of secondary outcomes and data collection methods for the effectiveness aim

Outcome domain	Outcome measure	Data collection	Assessment modality
**Global pain***	Musculoskeletal pain	Musculoskeletal pain intensity and localisation	Nordic-style questionnaire†
	Overall pain	Self-rated overall pain	Numerical Rating Scale†
	Quality of life	Quality of life score	FACT-B†, FACT-ES†
	Fatigue	Fatigue score	FACIT – Fatigue†
	Anxiety	Anxiety and depression scores	HADS†
**Cognitive function**		Perceived cognitive impairments	FACT-Cog†
**Physical condition**	Respiratory function	FEV1, PEF, VT, VC, RV, TLC, DLCO	Pulmonary function tests
	Cardiac function	VO₂ peak, VO₂ max, maximal heart rate, VO₂ at VT1, cardiac output at VT1, heart rate at VT1, blood pressure, oxygen saturation	Cardiopulmonary exercise test
	Cardiorespiratory endurance	Distance walked in 6 minutes	6-minute walk test
	Muscular strength	Isometric grip strength	Handgrip strength test
	PA level	Habitual levels of PA	Marshall questionnaire†, IPAQ†
**Body composition**	Anthropometric measurements	Body weight, height, body mass index, waist circumference and 4-site skinfold	Anthropometric assessment
	Malnutrition	MUST score	MUST†
**Evolution of a metabolic syndrome**		Waist circumference	Anthropometric assessment
		Blood pressure	Blood pressure measurement
		Lipid profile, assessment of insulin resistance and inflammatory status	Blood tests: lipid profile, HOMA-IR, C-reactive protein
**HRV‡**		HRV parameters	24-hour Holter ECG recording
**Therapeutic adherence to the AI**		Therapeutic adherence to the AI	Girerd self-assessment questionnaire†
**Adverse events related to APA**		Adverse events related to APA sessions	Participant self-report

* The evaluation of AIMSS requires a structured and multidimensional approach. It will include a targeted assessment of musculoskeletal pain, a self-report of overall perceived pain and an analysis of its psychosocial impact.

† Self-Report Questionnaires.

‡ Heart rate variability is a non-invasive indicator of autonomic cardiac regulation, reflecting the balance between sympathetic and parasympathetic activity. A decrease in HRV has been associated with increased clinical vulnerability in oncology. Several studies have reported associations between altered HRV and clinical parameters such as fatigue, pain and tumour progression.

.AI, aromatase inhibitor; AIMSS, AI-associated musculoskeletal syndrome; APA, adapted physical activity; DLCO, diffusing capacity of the lung for carbon monoxide; FACIT-Fatigue, Functional Assessment of Chronic Illness Therapy – Fatigue; FACT-B, Functional Assessment of Cancer Therapy – Breast; FACT-Cog, Functional Assessment of Cancer Therapy - Cognitive Function; FACT-ES, Functional Assessment of Cancer Therapy - Endocrine Symptoms; FEV1, forced expiratory volume in 1 s; HADS, Hospital Anxiety and Depression Scale; HOMA-IR, Homeostatic Model Assessment for Insulin Resistance; HRV, heart rate variability; IPAQ, International Physical Activity Questionnaire; MUST, Malnutrition Universal Screening Tool; MUST, Malnutrition Universal Screening Tool; PA, physical activity; PEF, peak expiratory flow; RV, residual volume; TLC, total lung capacity; VC, vital capacity; VO_2_ max, maximal oxygen consumption; VO_2_ peak, peak oxygen consumption; VT1, ventilatory threshold 1; VT, tidal volume.

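### T2 lipids, follow-up glucose/insulin and CRP are taken only in selected women, and pulmonary function only at baseline, yet all are effectiveness outcomes with planned between-arm comparisons

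*Protocol article*

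**What the plan says.** All references are to the protocol article.

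**Outcomes.** The section on secondary outcomes for the effectiveness aim includes physical condition and indicators of metabolic syndrome, and states: "These outcomes will be assessed at four time points (T0, T1, T_APA_, T2"). Table 2 places "Lipid profile, assessment of insulin resistance and inflammatory status" under the metabolic syndrome domain (lipid profile, HOMA-IR, C-reactive protein). It lists respiratory function, measured by pulmonary function tests, under physical condition.

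**Analysis.** The quantitative analysis section works in the intention-to-treat population. For the secondary objectives it plans "between-group comparisons at specific time points (T0, T1, T_APA_, T2"), between-group comparisons of change (T0–T1 and T1–T2 are its examples) and within-group change.

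**Schedule.** The blood-test footnote to Table 1 begins "lipid profile at V0 and V1 (V2 if abnormal value at V1), fasting insulin and fasting blood glucose at V0". Item by item, Table 1 and this footnote say:
- Lipids: "lipid profile at V0 and V1 (V2 if abnormal value at V1").
- Insulin and glucose, from which HOMA-IR is computed: "fasting insulin and fasting blood glucose at V0 (V1 if abnormal value at V0 and V2 if persistent abnormal value at V1").
- CRP: "C-reactive protein at V0 (V1 and V2 if inflammation is suspected").
- The blood-test row has no mark at T_APA.
- The row "Pulmonary function test" is marked at T0 only.
- Cardiopulmonary exercise testing and Holter are marked at T0 and T2, without condition.

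The footnote's V0, V1 and V2 are not in the abbreviation list. I read them as T0, T1 and T2, which fits the marks in the blood-test row.

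**The concern.** An intention-to-treat comparison at a visit needs the value from every randomised woman, or at least a reason for absence that is unrelated to the arm. Here the schedule itself decides who is measured. In the experimental arm the programme starts at T0, so a T1 value is post-randomisation and the intervention can change it. A woman whose lipids the programme has normalised by T1 supplies no T2 lipid value, while a comparable control who remains abnormal does. The women retested in the two arms are then no longer comparable groups, and the benefit being sought helps decide who is observed.

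CRP follow-up depends on someone suspecting inflammation, in a trial described as open-label. Glucose and insulin are never repeated in a woman normal at T0, so new insulin resistance in her cannot be seen. Respiratory function, a named effectiveness outcome, has nothing to compare after baseline.

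**Working it through.** **1. Status of each measure, from Table 1**

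| Measure | T1 | T_APA | T2 |
|---|---|---|---|
| Lipids | all women | none | only if abnormal at T1: selected after randomisation |
| Insulin/glucose | only if abnormal at T0: baseline-defined subgroup | none | only if still abnormal at T1: selected after randomisation |
| CRP | only on suspicion: selected after randomisation | none | as T1 |
| Pulmonary function | none | none | none |
| Exercise test, Holter | none | none | all women |
| Waist | all women | all women | all women |

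The T0 work-up precedes any treatment, so selection on a T0 value is selection on a baseline variable. The end-of-study visit section names exercise testing and Holter as the additions at T2 and does not name pulmonary function.

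**2. The plan's own figure.** The protocol gives no calculation for these outcomes. Its primary sample size (40% vs 20%, two-sided 5%, 80% power) reproduces with pooled variance: [1.96·√(2·0.3·0.7) + 0.842·√(0.4·0.6 + 0.2·0.8)]² / 0.2² ≈ 81.2, so 82 per arm; 164/0.9 = 182.2, against 182 stated. This point does not depend on it. I use 82 per arm only as a scale.

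**3. Illustration for T2 lipids.** Nothing in the documents gives these inputs; they are assumptions.
- Normal values with SD 1; abnormal at T1 in 40% of controls and 25% of the experimental arm.
- True T1 shift: cut-offs 0.253 and 0.674 SD above the arm means, so 0.674 − 0.253 = 0.421 SD.
- Women retested, out of 82 per arm: 0.40 × 82 = 32.8 and 0.25 × 82 = 20.5.
- Mean T1 value of retested women above their own arm's mean, λ = φ(cut-off)/share: 0.386/0.40 = 0.966 (control) and 0.318/0.25 = 1.271 (experimental). The difference is 0.305.
- With T1–T2 correlation ρ and true T2 difference δ, the difference among retested women is δ + 0.305ρ.

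If the full effect persists to T2 (δ = −0.421):
- ρ = 0.6: −0.421 + 0.183 = −0.238 SD
- ρ = 0.8: −0.421 + 0.244 = −0.177 SD

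If the arms have converged by T2 (δ = 0), the same formula gives +0.183 and +0.244 SD, an apparent disadvantage for the experimental arm where none exists.

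A simulation with other assumptions (control abnormality 20%, 30% or 50%, ρ = 0.7, persisting effect −0.5 SD) gave −0.21, −0.23 and −0.26 SD among retested women. About 16 vs 7, 25 vs 12–13 and 41 vs 25 of 82 were tested, control vs experimental.

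**4. T1 insulin/glucose.** Here the loss is of coverage and precision. The detectable difference at 80% power is (1.96 + 0.842)·√(2/n) per arm. If 20%, 30% or 50% of women were abnormal at T0 (assumed), n = 16, 25 or 41 gives 0.99, 0.79 or 0.62 SD, against 0.44 SD with all 82.

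**The case against.** **The general wording is only a summary.** The sentence on four time points mentions questionnaires, clinical examinations and functional tests, not blood tests, and the analysis section names no lipid, HOMA-IR, CRP or spirometry contrast. Table 1 is the specific schedule. That softens the contradiction but does not remove it: Table 2 lists these markers as effectiveness outcomes, and the analysis section offers no other treatment for them.

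**The missing values are explained by recorded data.** Retesting of lipids and of insulin/glucose depends on a recorded earlier value, so the values are missing at random by design, and the protocol promises appropriate handling of missing data. In a simulation of the scenario above, regressing T2 on T1 lipids and standardising to all women recovered −0.42 SD at ρ of 0.6 and 0.8. This stands for lipids as a sensitivity analysis. It relies on linear extrapolation below the threshold, where no T2 value exists, and its standard error was about 0.22–0.26, against √(2/82) = 0.16 with complete data. It does not help CRP, pulmonary function or women normal at T0 who are never retested for glucose or insulin, and the analysis section does not state it.

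**Stronger readings that the documents do not support.** A reader might infer that:
- T1 lipids are selected too. They are taken in everyone, so the T1 and T0–T1 lipid comparisons are valid.
- T1 glucose/insulin is selected by a post-randomisation result. The trigger is the T0 value, so it is a baseline subgroup.
- New metabolic syndrome cannot be detected at all. Waist, one of the domain's components, is measured in everyone at every visit, and the protocol gives no definition of the syndrome from which such a claim could follow.
- Exercise testing and Holter are also defective. They are taken in everyone at T0 and T2, which supports a valid comparison.
- A fixed share of the effect is lost. Controls start the same programme at T1, so the T2 effect may shrink, and the size of the bias depends on assumptions outside the documents.

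**Conclusion.** The point holds in this limited form. Followed as written, Table 1 cannot supply the comparisons that the outcome and analysis sections promise for four sets of secondary outcomes. T2 lipids, T2 insulin/glucose and T1/T2 CRP would be compared in women selected after randomisation, by values or suspicion that the intervention can influence. T1 insulin/glucose is limited to women abnormal at baseline. Respiratory function has no post-baseline value.

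The structural part rests on the documents alone, given the reading of V0–V2 as T0–T2. The size does not: 0.18–0.24 SD seen in place of 0.42 SD is an illustration that assumes 40% vs 25% abnormal at T1, normality, correlation 0.6–0.8 and an effect that persists after controls begin the programme. The primary outcome and sample size are unaffected, so this should be corrected but does not threaten the main result.

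**What to change.** 1. Limit confirmatory between-arm comparisons to values taken in everyone: lipids T0 to T1; waist at all visits; blood pressure at the visits where it is scheduled for all (Table 1 names it only within exercise testing, at T0 and T2); exercise testing and Holter T0 to T2.
2. Report T2 lipids, follow-up insulin, glucose and HOMA-IR, and follow-up CRP descriptively as clinical follow-up. For lipids only, a sensitivity analysis modelling T2 on the T1 value in all women could be added, with its extrapolation stated.
3. Move pulmonary function from the Table 2 outcomes to the baseline characteristics.
4. Correct the statement on four time points, and the comparisons in the quantitative analysis section, to the Table 1 schedule, and use one set of visit labels.
5. Optional: if evolution of metabolic syndrome at T2 is to remain an outcome, the same blood panel would have to be measured in every woman at T2.

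Items 1 to 4 cost wording and a shorter list of claimed secondary outcomes. Item 5 costs a complete T2 blood panel for every woman.

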#### Initial assessment/randomisation (T0)

A clinical and paraclinical examination by the multidisciplinary sports medicine team during a day care hospital visit, before any therapeutic intervention, will include clinical data, cardiopulmonary exercise testing, pulmonary function testing, 24-hour Holter ECG monitoring, additional examinations and Self-Report Questionnaires. Patients will also be instructed on daily PA self-monitoring via an electronic or paper logbook. The estimated completion time is 2 min per day.

They will be randomised into two groups.

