#### End-of-study visit (T2)

The end of the study will be defined as 6 months after the initiation of AI therapy, which corresponds to the median time point at which both the peak of AIMSS symptoms and treatment discontinuation due to AIMSS are reported in the literature.^19^ This assessment will follow the same procedure as T1 and T_APA_, with the addition of cardiopulmonary exercise testing and 24-hour Holter ECG monitoring.

Semi-structured individual interviews will be conducted by two researchers with patients and healthcare professionals.

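### Total spectral power, the only heart rate variability parameter named, can show a fall in overall variability but cannot attribute a change to either autonomic branch or show their balance

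*Protocol article*

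**What the plan says.** HRV is a secondary effectiveness outcome, taken from a 24-hour Holter recording at T0 and T2 (Table 1).

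- **Table 1, Holter footnote:** one parameter is named, "24-hour Holter ECG monitoring: total spectral power".
- **Table 2, HRV row:** the data to be collected are "HRV parameters", in the plural and without a list.
- **Table 2, HRV footnote:** "Heart rate variability is a non-invasive indicator of autonomic cardiac regulation, reflecting the balance between sympathetic and parasympathetic activity". The next sentence adds a second rationale: "A decrease in HRV has been associated with increased clinical vulnerability in oncology". The footnote then mentions reported links between altered HRV and fatigue, pain and tumour progression.
- **Initial assessment/randomisation (T0):** the examination takes place "during a day care hospital visit, before any therapeutic intervention, will include clinical data, cardiopulmonary exercise testing, pulmonary function testing, 24-hour Holter ECG monitoring".
- **End-of-study visit (T2):** the visit repeats the earlier procedure "with the addition of cardiopulmonary exercise testing and 24-hour Holter ECG monitoring". Neither section gives the order of the two tests or the gap between them.
- **Quantitative data analysis:** secondary outcomes are compared between groups at time points and as change over time. Adjustment for the T0 value is not mentioned.

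**The concern.** The parameter in Table 1 and the first meaning given in Table 2's footnote do not match. Total power adds up all frequency bands. If the trial reports an arm difference in total power, a reader of the footnote may take it as a shift between sympathetic and parasympathetic activity, which the number cannot show. If the trial reports no difference, the same reader may conclude that autonomic balance was unaffected, which does not follow either.

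The tables also leave it unclear which parameters are planned. The neighbouring Table 1 footnotes itemise their measures (seven entries for pulmonary function, eight for the cardiopulmonary exercise test), and Table 2 largely repeats those lists. For HRV, one table gives a single parameter and the other an open plural. An index chosen after the recordings have been seen would carry less weight than one named now.

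**Working it through.** **No HRV figure to reproduce.** The only design calculation in the article is the primary sample size. With 40% against 20%, two-sided 5% alpha, 80% power, pooled variance and no continuity correction, the formula gives 82 per arm, as stated. HRV does not enter it.

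**Extent.** 182 women × 2 recordings (T0, T2) = 364 recordings at most.

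**What a total can and cannot show.** Write total power as TP = VLF + LF + HF, with everything below the low-frequency band placed in VLF. The band values below are assumed for illustration; the article gives none.

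| Spectrum | VLF | LF | HF | TP (ms²) | LF/HF |
|---|---|---|---|---|---|
| A | 1000 | 800 | 200 | 1000 + 800 + 200 = 2000 | 800/200 = 4.0 |
| B | 1000 | 200 | 800 | 1000 + 200 + 800 = 2000 | 200/800 = 0.25 |

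1. *Balance.* A and B differ widely in how power is divided, yet the difference in TP is 2000 − 2000 = 0.
2. *Attribution.* Start from A and remove an amount d. Taken from LF or from HF, the result is the same: TP = 2000 − d. A change in TP does not say which band moved.
3. *Overall variability.* If all bands fall, TP falls. For the rationale based on a decrease in HRV, TP is a suitable measure.

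**Would a vagal index settle balance?** No. HF power (or RMSSD) is taken here, as an assumption from general usage, to index the vagal branch. One branch alone does not determine a relation between two. The index allows a statement about vagal activity and no more.

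**Comparison at T2.** Let ρ be the correlation between the T0 and T2 values, and assume equal variances at both times. In units of the T2 variance, the variance entering the between-arm comparison is:

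- T2 value alone: 1
- change from T0: 2(1 − ρ)
- T2 adjusted for T0: 1 − ρ²

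The adjusted form never exceeds the first, since ρ² ≥ 0. Nor does it exceed the second, since 2(1 − ρ) − (1 − ρ²) = (1 − ρ)² ≥ 0. So for any ρ the adjusted comparison is at least as precise as either comparison the article lists, apart from the negligible cost of estimating one slope. The T0 value is already collected.

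**Holter and exercise test.** T0 and T2 each contain both tests. With no order stated, a 24-hour recording may include the test, follow it, or precede it. The schedule is the same for both arms.

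**The case against.** The strongest reply is that the article does not tie the outcome to autonomic balance alone. The objectives and the analysis section state no hypothesis about balance, and the footnote goes on to give decreased HRV as its clinical rationale, which total power serves. This stands. It means total power should be kept and that only the balance reading is unsupported.

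A second reply is that Table 2 uses the plural and that a condensed article may leave the full list of Holter indices to the full protocol. This also stands in part. A reader might infer that total power is the only index that will be extracted and that the rest of the recording is thrown away; the article shows only that it is the one index named. What remains is that the two tables do not agree on what is planned.

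A third reply concerns the exercise test. A reader might infer that the test contaminates the recording and biases the comparison. The documents do not support that: order and overlap are not stated, and the arrangement is common to both arms. Only the request to fix the order, or to leave the test period out of the vagal segment, survives.

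Finally, the equal and opposite band changes in the illustration are invented. They show what a sum cannot determine; they do not predict what the trial will see.

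**Conclusion.** The point holds as a minor one. Total power, the one HRV parameter named, fits one of the two meanings given in Table 2's footnote (overall variability) and not the other (balance between branches). Used alone it cannot attribute a change to either branch, and Tables 1 and 2 should state the same parameters.

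Two stronger conclusions are tempting and should not be drawn: that the HRV outcome as a whole is uninformative, and that the shared visit with the exercise test biases the arms. The footnote's second rationale rules out the first, and nothing in the text establishes the second.

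The algebra rests on total power being the sum of its bands and, for the precision argument, on equal variances at T0 and T2. The vagal reading of HF power or RMSSD is an assumption. At most 364 recordings are concerned.

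**What to change.** 1. Keep 24-hour total power as the measure of overall HRV.
2. Pre-name one vagal index from the same recordings, either high-frequency power or RMSSD, as an exploratory HRV outcome. List it with total power in both Table 1's footnote and Table 2.
3. Limit claims to overall variability and vagal activity, and adjust the footnote so that it does not promise a measure of balance.
4. Compare arms at T2 adjusted for the T0 value.
5. State the order of the Holter and the exercise test and keep it the same at T0 and T2, or exclude the test period from the segment analysed for the vagal index.

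The cost is one more exploratory variable, some extra output from the Holter software, and wording changes in two tables. No visit, recording or patient is added.
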